#### Economic evaluation

A costing study will be conducted to estimate the total costs of developing, setting up and running the Y-Check package, in school and community settings. A combination of top-down and ingredients-based costing approaches will be used to generate cost estimates for the whole package, and for each component/activity. All costs will be estimated from the perspectives of the adolescents, the schools/community and implementing partners/service providers. Financial and economic costs will be calculated for all inputs. These inputs will be identified and measured using process data, staff interviews and observations, document review and accounting records.

Costs will be inputted and analysed in an Excel-based costing tool. The cost analysis will describe the distribution of costs across different forms of inputs, and will estimate the unit cost per adolescent reached, screened and treated on the spot or referred; cost per unit of measure for selected process and effect outcomes such as cost per condition detected, cost per condition appropriately treated on-the-spot or with a completed referral within 4 months, cost for a unit improvement in reported quality of life and Disability Adjusted Life Years averted.

The cost and cost-effectiveness estimates will be compared with other programmes in the region (eg, human papillomavirus vaccination and deworming) and will inform programme replication, scalability and financial sustainability.

#### Data protections

Data protection will be strictly observed. After study completion, data will be stored in the LSHTM-curated digital repository ‘Data Compass’ following General Data Protection Regulation (GDPR) guidelines. Data and code registered in LSHTM Data Compass will be made open access following deposit. A Data Safety and Monitoring Board (DSMB) has been constituted to assist in managing adverse events, though we expect these to be very rare since all treatment and care are standard with no novel treatments.

### Study outcomes

Outcomes will be ascertained during the check-up screening visit and through collection of referral vouchers from the referral health facilities, and, for outcomes related to health and well-being impacts, through data from the 4 month and, in Zimbabwe only, 12 month follow-up visits. Outcomes related to completed referrals will be triangulated against participants’ self-reports at the 4 month and in Zimbabwe only, 12 month follow-up visits. Review of school and health service registers will be used to see whether attendance has increased during the period when Y-Check is being implemented.

The primary outcome will be the proportion of those screening positive for at least one condition who receive appropriate on-the-spot care or complete appropriate referral for all identified conditions within 4 months. This will be measured using data collected at the initial check-up visit and through recovery of referral vouchers given to participants to allow them to access referral services for free during the 4 months after the Y-Check screening. Completed referral is defined as attending at least the first referral appointment.

Secondary implementation outcomes will include the proportion of those screening positive for each condition who receive appropriate on-the-spot care or complete appropriate referral for that condition within 4 months, the yield of previously untreated conditions, clinical outcomes at 4 months among those who had originally screened positive for each condition, and intervention acceptability, adoption, appropriateness, feasibility, fidelity and cost. Secondary effectiveness outcomes will include knowledge about health services and health behaviours, self-reported agency and self-efficacy to make decisions about their health, self-reported health-related risk and protective behaviours, reported engagement with health services, well-being, self-esteem and quality of life, clinical outcomes and educational outcomes, which will be collected within the Y-Check and follow-up visits. The short-term cost-effectiveness of the intervention will be estimated (calculated by a comparison of the costs of the intervention against the primary and secondary outcomes and including short-term changes in self-reported quality of life). All outcomes for the study are described in table 3.

**Table 3 T3:** Study outcomes and means of verification

Outcome	Sources of data
**Primary outcome**	
Proportion of those screening positive for at least one condition who receive appropriate on-the-spot care or complete appropriate referral for all identified conditions within 4 months (ie, they attend a provider for referral care who has been accredited by the study team and has been shown to be capable of providing appropriate referral care).	Programme monitoring data including records of attendance for referrals. Screening tool (self-reported symptoms or conditions, measurements and clinical actions).
**Secondary outcomes**	
**Implementation outcomes**	
Proportion of those screening positive for each condition who receive appropriate on-the-spot care or complete appropriate referral for that condition within 4 months.	Programme monitoring data including records of attendance for referrals Screening tool (self-reported symptoms or conditions, measurements and clinical actions).
The yield of previously untreated conditions.	Programme monitoring data including records of attendance for referrals. Screening tool (self-reported symptoms or conditions, measurements and clinical actions).
Intervention acceptability (satisfaction): acceptability to adolescents and to other stakeholders (eg, schools, parents and health workers).	Programme monitoring data including records of attendance for referrals. Screening tool (self-reported symptoms or conditions, measurements and clinical actions). Self-completed evaluation questionnaire. Exit interviews. Observations of the Y-Check visits and of selected referrals. Interviews and workshops with adolescents, healthcare providers, community members, teachers, parents and key stakeholders.
Intervention adoption (uptake, utilisation): Y-Check uptake, referrals completed.	
Intervention appropriateness (perceived fit, perceived relevance and perceived usefulness): perceived value of the intervention to adolescents and to other stakeholders.	
Intervention feasibility (actual fit, practicability): Y-Check visits completed, referrals completed, stakeholder support (including community).	
Intervention fidelity (adherence, integrity, quality): completeness of training for and delivery of intervention components; diagnostic accuracy; youth-friendly health services quality assessment.	Interviews and workshops with adolescents, healthcare providers, community members, teachers, parents and key stakeholders. Observations of the Y-Check visits and of selected referrals, including youth friendly services. Self-reported screening tool
**Economic outcomes**	
Cost of setting up and running the intervention.	Y-Check documentation and financial records Interviews with Y-Check staff and staff of the referral facilities. Programme monitoring data including records of attendance for referrals. Screening tool (self-reported symptoms or conditions, measurements and clinical actions).
Cost per adolescent with a newly diagnosed condition (overall and by condition).	
Cost per adolescent with a newly diagnosed condition who received appropriate on-the-spot care or who completed an appropriate referral within 4 months (overall and by condition).	
Short-term (4 months) cost-effectiveness: cost per improvement in health or well-being (eg, cost per case addressed or cured), cost per unit improvement in QALYs and per DALY averted.	
**Client outcomes**	
Knowledge about health services and health behaviours.	Programme monitoring data including records of attendance for referrals. Screening tool (self-reported symptoms or conditions, measurements and clinical actions). Self-completed evaluation questionnaire.
Intentions to adopt healthy behaviours.	
Agency to make decisions about health and well-being.	
Perceived social support for behaviour change.	
Health-related risk and protective behaviours.	
Improvement in previously diagnosed health and well-being conditions.	
Engagement with health and other services within the past 4 months.	
Self-esteem.	
Self-perceived well-being.	
Quality of life.	
Clinical outcomes.	
Educational outcomes (eg, school attendance).	Self-completed evaluation questionnaire. School register review.
Client-defined outcomes (to be determined).	Self-completed evaluation questionnaire. Exit interviews.

DALYs, Disability Adjusted Life Years; QALYs, Quality Adjusted Life Years.

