### The Y-Check intervention

Y-Check is a novel intervention delivering a health and well-being check-up and, where indicated, will provide on-the-spot care and/or referral for common conditions on two occasions in adolescence (in young adolescents (10–14 year olds)—soon after the onset of puberty—and in older adolescents (15–19 year olds)—when many adolescents become, or are soon to become, sexually active). It will also provide health promotion information and materials to support positive behaviours and healthy lifestyles during adolescence and beyond. The intention is that in the context of a future routinely delivered programme, every adolescent will have two guaranteed contacts with the healthcare system. Adolescents will only be screened for conditions that have an accurate, low-cost, acceptable screening test and a locally accessible, effective intervention. The conditions selected for screening will be chosen to reflect the local epidemiological contexts (eg, screening for malaria will only take place in malaria endemic areas). Respecting specific requests from the Ministries of Education in all three cities, the study will only include SRH screening and services at the community sites (which only include older adolescents).

Figures 1 and 2 present the Theory of Change and description of the intervention. Table 1 applies the Template for Intervention Description and Replication (TIDieR) checklist^18^ to describe details of the intervention.

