**Figure 2 F2:**
[figure not shown]
The Y-Check intervention package. *The intervention package may vary according to setting.

**Table 1 T1:** Template for Intervention Description and Replication (TIDieR) checklist describing the Y-Check intervention

Item	Item
Brief name	
1	Evaluating the effectiveness of adolescent health check-ups (Y-Check)
Why?	
2	Identifying adolescents with poor health, health-compromising behaviours or undiagnosed disability is important for their health and well-being, and also for communities and nations Most adolescents only come into contact with health services when they are ill, and services are not always appropriate for their needs Routine health and well-being check-up visits for adolescents that screen for multiple preventable and/or treatable conditions and risk behaviours could provide an entry point into services and be highly cost-effective
What?	
3	The intervention includes a comprehensive health check-up for priority conditions customised to national and local contexts. Where indicated, Y-Check will provide on-the-spot care and cover all clinical costs associated with referrals to further care provided by the public health system or non-governmental organisations (NGOs). During the check-up, adolescents will receive health promotion information and limited supplies of key health commodities. Clinical costs of services are covered by the study if accessed within 4 months of the check-up.
4	Adolescent-friendly services will be provided, as defined by WHO (2018). Nationally approved protocols will be applied. Adolescent privacy and confidentiality will be protected.
Who provided?	
5	Y-Check teams will be staffed with health professionals trained to provide quality adolescent-friendly health services in line with nationally approved protocols. Y-Check teams will also be trained in the use of the digital application which will be used for data collection. Public and private not-for-profit care facilities providing referrals will meet national accreditation guidelines.
How?	
6	The Y-Check service will take place over a 60–90 min period face-to-face. Any referrals will only be subsidised by the study if they take place within 4 months.
Where?	

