
### Study design

In this prospective hybrid implementation-effectiveness study, 2000 adolescents per city who receive the Y-Check intervention will be followed up at 4 months, and at 12 months (Zimbabwe only).

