### Intervention implementation

The intervention will be delivered over a period of 2–6 months in each of the settings. The follow-up visits will take place at the same school or community setting as the initial check-up. In addition to covering all clinical costs, the equivalent of US$5 will be given to each participant who attends the follow-up to cover any transport costs that they might have incurred. Additionally, health and hygiene related items will also be provided for adolescents to take home, including tooth cleaning kit (toothbrush and toothpaste), fruit, bottle of water, two pairs of underpants and pack of reusable sanitary pads (girls only).

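### The 4-month service-engagement outcome covers the same 4 months as the study-paid voucher referrals, so a before–after rise cannot be read as changed self-initiated care-seeking

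*Protocol article*

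**What the plan says.** **The outcome.** Table 3 (Client outcomes) lists "Engagement with health and other services within the past 4 months". The Study outcomes section places reported engagement with health services among the secondary effectiveness outcomes and says that these are collected at the Y-Check visit and at follow-up.

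**Follow-up.** All three cities have a 4-month visit; Zimbabwe also has one at 12 months (Study design).

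**Study-paid care.** Table 1, item 3: "Clinical costs of services are covered by the study if accessed within 4 months of the check-up". The Study outcomes section describes "referral vouchers given to participants to allow them to access referral services for free during the 4 months after the Y-Check screening". Table 1, item 7 sends referrals to public or not-for-profit providers near the adolescent's home.

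**Analysis.** The Statistical analysis section compares outcomes measured at two or more time points before and after, takes baseline as the counterfactual and uses no contemporaneous comparison group.

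**Registers.** Study outcomes: "Review of school and health service registers will be used to see whether attendance has increased during the period when Y-Check is being implemented". Delivery is short: "The intervention will be delivered over a period of 2–6 months in each of the settings". The article names no comparison period for the registers.

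**Where referrals are already reported.** Table 3 lists completed referrals under both adoption and feasibility, and the Statistical analysis section reports referrals made and completed by age, sex and city.

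**The concern.** At baseline the look-back covers 4 months in which the participant had no Y-Check voucher. At the 4-month visit it covers the 4 months in which every referred participant held one. A participant who uses the voucher, and would otherwise have sought no care, moves from not engaged to engaged because the programme sent and paid for that visit. Nothing in the article keeps such visits apart from those the adolescent sought independently.

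The Background describes the wider aim as including the development of health-seeking behaviours, and the Objectives list engagement with health services as a short-term impact to be estimated. A rise in this outcome is likely to be read as evidence for both. As fixed, it cannot tell a lasting change in care-seeking from attendance at study-paid referrals.

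The argument given for having no comparison group does not help. It concerns falls in the prevalence of chronic conditions, not a utilisation measure whose follow-up value can contain the intervention itself.

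The health service registers have the same difficulty: during delivery they can contain the study's own referred patients. With a delivery period of 2–6 months and no named comparison period, season and school term can also move the register figures.

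**Working it through.** **1. The article's own figure.** The article gives no figure for engagement. Its planning example (Sample size) is 500 per age–sex group, 30% screening positive (150), 75% of those correctly managed, 95% CI ±7%. Check: 1.96 × √(0.75 × 0.25 / 150) = 1.96 × 0.0354 = 0.069, or 6.9 points. The ±7% reproduces. It does not bear on the engagement outcome, but the 30% and 75% can be used as inputs.

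**2. Share of participants with a programme-generated referral contact.** Let r be the share of correctly managed participants handled by referral rather than on the spot. The article does not give r. Then s = 0.30 × 0.75 × r = 0.225 × r.

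- r = 1: s = 22.5% (about 112 of 500 per group, 450 of 2000 per city)
- r = 0.5: s = 11.25%
- r = 0.25: s = 5.63%
- r = 0: s = 0

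The 22.5% is the ceiling among participants counted as correctly managed. Correct management requires all identified conditions to be dealt with, so someone with several conditions who attends for only some of them would add to it.

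**3. Built-in rise.** Let b be the proportion engaged in the 4 months before baseline (assumed; not in the article). Suppose self-initiated use is unchanged and is equally common among referred and other participants. Measured engagement at 4 months is then b + (1 − b)s, so the rise is (1 − b) × s:

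| Baseline b | r = 0.25 | r = 0.5 | r = 1 |
|---|---|---|---|
| 10% | 5.06 | 10.13 | 20.25 |
| 20% | 4.50 | 9.00 | 18.00 |
| 30% | 3.94 | 7.88 | 15.75 |
| 50% | 2.81 | 5.63 | 11.25 |

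(percentage points)

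The range is about 3 to 20 points with no change in self-initiated care-seeking, and zero at r = 0. If voucher contacts are excluded, this component is zero by definition.

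**4. The 12-month visit in Zimbabwe.** If the same item is asked there, its look-back covers months 8 to 12, after voucher cover has ended. The 4- and 12-month values would then measure different things unless voucher contacts are separated.

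**5. Registers.** Check-ups take place in schools and community venues, so facility registers would mainly pick up the referrals. On the rates above that is at most about 450 attendances by correctly managed participants per city, counting one each. In a large facility catchment this may be a small change. School attendance is not touched by vouchers; there the difficulty is only the unnamed comparison period.

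**The case against.** **Linkage to care is an intended effect.** The Background presents check-ups as an entry point into services, and engagement is a stated short-term impact. A measure that includes completed referrals is legitimate. This stands, and it is why voucher contacts should be shown separately rather than discarded. It does not make the combined figure evidence of changed care-seeking.

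**What counts as a contact belongs in the questionnaire or analysis plan.** Partly right: the item wording is not shown. But the article itself fixes the window, the voucher period and the uncontrolled comparison, and together these produce the overlap unless a rule removes it.

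**Referral records may not feed this outcome.** Table 3 gives "Programme monitoring data including records of attendance for referrals" as a source for the client outcomes, but the entry appears to span many rows, including ones such as self-esteem that cannot come from referral records, and Study outcomes calls engagement reported. This stands, so the point does not rest on that source. Self-report would also capture a voucher visit unless the question excludes it.

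**Referrals are already reported separately.** True, and it helps a reader. It does not allow the engagement change to be split, because the overlap with other contacts is needed at participant level.

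**Two stronger readings a reader might infer.** One is that engagement must reach 100% because the check-up itself is a contact. The article does say that "every adolescent will have two guaranteed contacts with the healthcare system", but about a future routine programme. Whether the check-up counts depends on wording not shown, and it falls at the edge of a 4-month look-back. The other is that the outcome counts the primary outcome a second time. It does not: the primary outcome is restricted to those screening positive, includes on-the-spot care and requires every identified condition to be managed, so numerator and denominator differ. The overlap is with completed referrals.

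**The registers are a side issue.** Table 3 ties register review only to educational outcomes, and a same-months comparison is not ruled out. The lack of a control is also disclosed among the limitations. These points limit the register concern to two gaps: no separation of voucher visits and no named comparison period.

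**Conclusion.** The concern holds as a matter of interpretation for one secondary effectiveness outcome. Because the 4-month look-back coincides with 4 months of study-paid referrals, part of any rise can be the programme's own referrals, and the rise cannot be attributed to self-initiated care-seeking.

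How large that part is cannot be fixed from the article. The 3–20 point range rests on the article's illustrative 30% and 75%, on assumed baseline engagement of 10–50%, and on an assumed 25–100% of managed cases handled by referral. The top of the range is an upper case, because the 75% includes on-the-spot care. The primary outcome, the sample size and the planned precision are unaffected. The change is worth making because it is cheap and alters what this outcome can conclude.

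**What to change.** 1. **Engagement outcome.** At follow-up, report two parts for each participant: (a) contacts other than the Y-Check visit and voucher-funded referrals, and (b) voucher-funded contacts. Compare (a) with baseline as the measure of health-seeking, and show (b) separately as programme linkage. The information is already collected: vouchers are recovered from facilities and checked against self-report at follow-up. Apply the same rule at 12 months in Zimbabwe.
2. **Health service registers.** Identify and subtract visits carrying a Y-Check voucher, and compare with the same calendar months of the previous year.
3. **School registers.** Compare attendance with the same term of the previous year.

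**Cost.** One derivation rule (and, if needed, one clarifying questionnaire item), modest extra extraction from registers already under review, and probably a smaller reported gain. Part (a) may understate self-initiated use where a voucher replaced a visit that would have happened anyway; showing both parts lets the reader see this.

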### Sample size

In each city, the intervention will be implemented for 10–14 year olds in up to six government primary schools (n=500 for young adolescent girls, and n=500 for young adolescent boys), and for 15–19 year-olds in up to eight secondary schools and up to three community venues (n=500 for older adolescent girls, and n=500 for older adolescent boys), giving a total sample size of 2000 adolescents (10–19 y).

The sample size provides specified precision around the primary outcome. For example, for the primary outcome, within each age group and gender, if 150 (30%) of 500 participants screen positive for at least one condition, and 75% of those who screen positive are correctly managed (n=112), the 95% CI for correct management will be ±7%. The primary outcome used data from the initial check-up visit and referrals and did not require the 4 month follow-up data.

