### Inclusion and exclusion criteria

To be included in the study, adolescents aged 10–19 years must fall into one of the first three categories below and fulfil category 4.

Be attending selected classes of year 5 of primary school in Mwanza (median age 11 years); grade 5/6 of primary school in Chitungwiza (median age 11 years) or year 1 of Junior Secondary School in Cape Coast (median age 12 years) ORBe attending selected classes in year 3 of Secondary School in Mwanza (median age 17 years), Form 3/4 in Chitungwiza (median age 17 years) or year 2 of Senior Secondary School in Cape Coast (median age 16 years) ORBe resident in a selected community during the time of the Y-Check intervention, and be aged 16–19 years

AND

Have a completed and signed Informed Consent form, or a signed Informed Assent Form and signed Parental/Guardian Informed Consent Form if the adolescent is seen in the community and is below the national age of consent or is seen in a school, irrespective of their age.

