### Statistical analysis

All primary analyses will be conducted separately by study city; Cape Coast, Chitungwiza and Mwanza. Where comparable, secondary analyses will be conducted with the data from all three cities combined.

In our study sites, a contemporaneous comparison group is not required since no routine screening is currently taking place, and as a result, assessments at baseline will serve as the counterfactual for internal comparisons. Similarly, since there is no routine screening and treatment provided to adolescents of the target ages in the study population, a before–after comparison is appropriate since it is plausible to assume that reductions in the prevalence of the chronic conditions between the original Y-Check visit and the follow-up at 4 months will be due to the interventions provided through Y-Check.

We will follow Strengthening the Reporting of Observational Studies in Epidemiology (STROBE) guidelines for the reporting of cohort studies. Descriptive analyses will be used to compare the community-level and school-level characteristics of the study communities and schools.

Quantitative programmatic data, including screening test results, services delivered and referrals made and completed will be reported by age, sex and city. The primary outcome is a single proportion which will be presented with a 95% CI for each of the four target groups: 10–14 year-old males, 10–14 year-old females, 15–19 year-old males 15–19 year-old females.

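### The ±7% precision for the primary outcome assumes independent participants, although each age-sex group in a city comes from a few schools and venues

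*Protocol article*

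**What the plan says.** The Sample size section justifies 500 participants per age-sex group in each city by precision alone. Its example is "if 150 (30%) of 500 participants screen positive for at least one condition", with 75% of those correctly managed (112), and it concludes that "the 95% CI for correct management will be ±7" per cent. It mentions no ICC, design effect or other allowance for site.

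The same section places the younger groups in "up to six government primary schools" and the older groups in "up to eight secondary schools and up to three community venues", per city. The inclusion criteria take school participants from chosen classes, for example "Be attending selected classes of year 5 of primary school in Mwanza".

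Under Statistical analysis, "The primary outcome is a single proportion which will be presented with a 95% CI for each of the four target groups", separately by city. Single-time-point secondary outcomes are to be presented in a similar way. School or community enters only the models for outcomes measured at two time points, as a fixed effect.

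Table 2 gives different site counts: Cape Coast has eight schools in total and four communities; Mwanza has up to eight primary schools, up to eight secondary schools and four to six communities. It gives no number of schools for Chitungwiza.

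**The concern.** The primary outcome counts a participant as a success only if every identified condition received on-the-spot care or a completed referral within 4 months. Participants at one school or venue share visit days and are likely to share nearby referral providers. Table 1 sends referrals as close to home as possible, and Table 2 says that Cape Coast deliberately includes two relatively affluent and two relatively poorer communities. Some between-site variation in referral completion is therefore foreseeable.

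With positive correlation within sites, 150 participants carry less information than 150 independent ones. The primary result is an estimate with an interval, and the ±7% is the only quantitative basis for the sample size. If it is optimistic, readers are promised more certainty than the design can give, in each of the four groups in each city.

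**Working it through.** **Inputs from the Sample size section.** n = 150 screen-positives per age-sex group per city; p = 0.75; at most k = 6 schools (younger) or 8 + 3 = 11 sites (older).

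**Assumptions.** The ICC is not given, so 0.01, 0.02 and 0.05 are used. Clusters are taken as equal in size and all permitted sites as used; fewer sites would make the loss larger.

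**Step 1: reproduce the stated figure.** Half-width under independence = 1.96 × √(p(1 − p)/n).
- p = 0.75: 1.96 × √(0.1875/150) = 6.93%.
- p = 112/150: 6.96%.

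A Wilson interval gives 6.90%. The arithmetic behind ±7% is right, and it corresponds to a design effect of exactly 1.

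**Step 2: allow for clustering.** DE = 1 + (m − 1) × ICC, with m = n/k; half-width = 6.93% × √DE. Here m = 150/6 = 25 and 150/11 = 13.6.

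| ICC | 6 schools: DE | half-width | 11 sites: DE | half-width |
|---|---|---|---|---|
| 0.01 | 1.24 | ±7.7% | 1.13 | ±7.4% |
| 0.02 | 1.48 | ±8.4% | 1.25 | ±7.8% |
| 0.05 | 2.20 | ±10.3% | 1.63 | ±8.9% |

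The half-width passes 7.5% at an ICC of about 0.007 with six schools and about 0.014 with eleven sites.

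**Step 3: critical value for few clusters.** With t on k − 1 degrees of freedom (2.57 for 5 df, 2.23 for 10 df) in place of 1.96:
- Six schools: ±11.1% at ICC 0.02; ±13.5% at ICC 0.05.
- Eleven sites: ±8.8% at ICC 0.02; ±10.1% at ICC 0.05.

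**Step 4: coverage if a plain binomial interval were reported.** Coverage = 2Φ(1.96/√DE) − 1. At ICC 0.05 this is 81.4% with six schools and 87.5% with eleven sites, against a nominal 95%.

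**Step 5: sensitivity to the site counts in Table 2 (normal critical value, ICC 0.05).**
- Eight primary schools, as Mwanza allows: m = 150/8 = 18.75, DE = 1 + 17.75 × 0.05 = 1.89, half-width ±9.5%.
- Four schools for the younger groups in Cape Coast (an assumed even split of its eight): m = 150/4 = 37.5, DE = 1 + 36.5 × 0.05 = 2.825, half-width 6.93% × 1.681 = ±11.6%.

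**Step 6: could larger numbers at the same schools restore ±7%?** The effective sample size, n/DE, cannot exceed k/ICC however large n becomes. With six schools and ICC 0.05 that limit is 6/0.05 = 120, below the 150 that ±7% needs.

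**The case against.** **The analysis plan may already use a clustered interval.** This stands in part. A reader might infer that the published 95% intervals will be too narrow. The article does not support that: calling the outcome a single proportion describes the outcome, not the variance estimator, and an article may leave the estimator to a document not shown here. Under-coverage is therefore conditional on a plain binomial interval. The ±7% itself is stated in the article, and a clustered interval would be expected to be wider.

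**Whole classes are not necessarily enrolled.** Correct. A reader might infer whole-class enrolment, but the criteria speak of selected classes with individual assent or consent, and community participants do not come by class. Clustering by site does not need whole classes.

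**The ICC is assumed, and the loss may be small.** Also correct: at 0.01 the half-width is within a percentage point of the stated one. The size of the shortfall is uncertain; its direction is not, for any positive ICC.

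**The sites are fixed.** Mwanza communities are purposively selected, and school enters the two-time-point models as a fixed effect. If inference were confined to these sites, between-site variation would add less. The article does not confine it so, and the Objectives say the study should supply parameters, including acceptability of referral, for planning a later evaluation.

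**Later sample sizes.** A reader might also infer that the next phase would be planned on this over-precise interval. The Discussion says those calculations will use short-term changes in clinical and behavioural outcomes, which are analysed differently, so that consequence is not shown.

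**It is only an example, with no test attached.** True: no success threshold depends on the interval, and the point estimate is unaffected. But no other figure supports 500 per group.

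**Conclusion.** The concern holds as a fault in the assumption, not in the arithmetic. The stated ±7% is the independent-participant half-width applied to a design with at most six or eleven recruitment sites per group in a city, and it is optimistic for any positive ICC. For assumed ICCs from 0.01 to 0.05 the shortfall runs from under one percentage point to about three with the normal critical value, and to more than six with six schools and a t reference (±13.5% against ±7%). These figures rest on the assumed ICC, equal cluster sizes, the maximum site counts in the Sample size section, and inference that extends beyond the selected sites. What the article does not establish is that the reported intervals will under-cover, because the interval method is not named.

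**What to change.** 1. In Sample size, say that ±7% assumes independence, and restate the expected half-width over a stated ICC range.
2. Base this on each city's own site counts, after reconciling the Sample size section with Table 2 (up to six primary schools per city against up to eight in Mwanza; up to three venues against four or more communities in Cape Coast and Mwanza).
3. Use the same critical value in the precision statement as in the analysis. Quoting about ±8% to ±10% for six schools while analysing with t on 5 degrees of freedom (±11.1% to ±13.5% for ICC 0.02 to 0.05) would again overstate precision.
4. Specify, for the primary outcome and the single-time-point proportions, a confidence interval clustered on school or venue with a small-cluster correction, and report the estimated ICC.

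The cost is a few sentences, a different interval command and a less favourable stated precision. No extra participants are needed.
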